#### Secondary outcomes

The method described above for the primary outcome will also be used for the percentages of patients with EEG evidence of an ongoing epileptic seizure between 6 and 12 h or of refractory SE after randomisation; ICU, hospital, and 90-day mortality; and 90-day functional impairments.

To compare seizure duration (in minutes), we will build a semi-parametric regression model (Cox or Fine–Gray) appropriate for an analysis of competing risks (control of SE vs. death without control of SE). This approach will be used also for ICU and hospital stay lengths (alive at ICU or hospital discharge vs. death in the ICU or hospital, respectively).

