#### Secondary outcomes

Secondary outcomes are as follows:Percentages of patients with recurrent convulsive and/or non-convulsive seizures between 6 and 12 h after randomisationTotal seizure duration in minutesPercentage of patients with refractory status epilepticusMortality in the ICU, in the hospital, and by day 90Total ICU and hospital stay lengths in daysPercentages of patients with functional impairments on day 90: frequency of seizures, recurrence of status epilepticus after discharge, number of antiepileptic drugs, MMSE score, and FIM score

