### Sample size

The working hypothesis for this randomised controlled trial is that, compared to standard care alone, standard care combined with therapeutic hypothermia increases the proportion of patients with a good 90-day outcome defined as a GOS score of 5. Assuming that 40 % of patients will have a GOS score of 5 on day 90 in the standard care group [4] and that this percentage will increase by 20 % (to 60 %) with therapeutic hypothermia, with a 5 % two-sided type I error rate, 90 % power, and a single interim analysis performed according to the O’Brien-Fleming method, 135 patients are needed in each group (270 patients in all).

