#### Primary outcome

The primary outcome will be assessed by using logistic regression to compare the percentage of patients with a 90-day GOS score lower than 5 in the two study groups. If needed, the logistic regression model will be adjusted to allow a more accurate assessment of the effect.

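### Day-90 MMSE, FIM and number of antiepileptic drugs are collected as graded values but are to be compared as percentages impaired, at a modest cost in power

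*Protocol article*

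**What the plan says.** All references are to the protocol article.

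- **Study outcomes, Secondary outcomes.** The day-90 functional outcome is expressed as percentages of patients with functional impairments. The items under it are seizure frequency, recurrence of status epilepticus, "number of antiepileptic drugs, MMSE score, and FIM score".
- **Statistical methods, Secondary outcomes.** "The method described above for the primary outcome will also be used for the percentages of patients" with several outcomes, the last of which is 90-day functional impairments.
- **Statistical methods, Primary outcome.** The method referred to is this: "The primary outcome will be assessed by using logistic regression to compare the percentage of patients" with a 90-day GOS score below 5.
- **Data collection and follow-up; Modalities of outcome evaluation.** MMSE and FIM are recorded as scores. The neurologist also records the frequency of recurrent seizures and the nature and dosage of antiepileptic drugs.
- **Statistical methods, Secondary outcomes (second paragraph).** Seizure duration and lengths of stay keep their own scale, through Cox or Fine–Gray models.

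The article gives no reason for reducing the functional scores to percentages.

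**The concern.** Recurrence of status epilepticus is a yes/no outcome and suits logistic regression. MMSE and FIM have many levels, and the number of drugs is a count. Splitting them at a threshold treats all patients on one side as equal and discards the ordering within each side.

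The section on aims makes reduction of 90-day motor and/or cognitive impairment and epilepsy a secondary objective. MMSE and FIM are the only listed day-90 measures of cognition and independence that are finer than the GOS. The primary outcome is already a two-way split of the GOS, so splitting these as well leaves no graded comparison of day-90 function. Numbers are also short: about 20 % of patients die in hospital (Background), and the day-90 visit takes place only where feasible (Table 1). Power lost to the scale of analysis is therefore worth recovering.

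**Working it through.** **1. The plan's own figure.** The Sample size section takes the share with GOS 5 at day 90 as 40 % for controls and 60 % for hypothermia. It sets the two-sided level at 5 % and power at 90 %, with one O'Brien-Fleming interim look.

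Pooled two-proportion formula, per arm: n = [1.960·√(2·0.5·0.5) + 1.282·√(0.4·0.6 + 0.6·0.4)]² / 0.2² = 129.3, so 130. The two-look O'Brien-Fleming inflation is 1.007, giving 130.9, so 131. With continuity correction the results are 140, and 141 with the inflation. The stated 135 per arm lies between these, and power at 135 is about 91 %. The primary calculation reproduces. No power is stated for the functional secondary outcomes.

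**2. Inputs for the secondary outcomes.**
- Scored per arm: not stated. About 135 × 0.80 = 108 survive at 20 % mortality. Range taken: 60 to 135.
- Effect: not stated. The plan's primary effect corresponds to an odds ratio of (0.6/0.4)/(0.4/0.6) = 2.25, or 2 × 0.253 = 0.51 SD on a latent normal scale.
- Distributions: not given, so assumed below.
- Two-sided 5 % level throughout.

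**3. Hand check of the order of magnitude.** Cutting at the median keeps a fraction 2/π = 0.637 of the information under a normal shift and 3/4 under proportional odds. Take a full-scale power of 80 %, so that the expected z is 1.960 + 0.842 = 2.802.
- Normal shift: 2.802 × √0.637 = 2.236; power = Φ(2.236 − 1.960) = 60.8 %; loss 19.2 points.
- Proportional odds: 2.802 × √0.75 = 2.426; power = Φ(2.426 − 1.960) = 67.9 %; loss 12.1 points.

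The first figure is for scores without a ceiling. MMSE and FIM have maxima, and ties at the maximum reduce what the full scale can add.

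**4. Normal shift with a ceiling.** Assumed MMSE: mean 25, SD 6, 23 % at the maximum. Assumed FIM: mean 110, SD 25, 27 % at the maximum. The rank test (the proportional-odds score test) was simulated against the 2×2 test. At 108 per arm and a 0.4 SD shift:

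| Scale | Full scale | Best of six cuts | Loss (points) |
|---|---|---|---|
| MMSE | 79.0 % | 63.2 % | 15.8 |
| FIM | 78.2 % | 63.2 % | 15.0 |

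Searching every MMSE cut by formula gives 64.6 % at best, a loss of 14.4 points. Across 60 to 108 per arm and shifts of 0.3 to 0.5 SD, the loss at the best cut is about 7 to 15 points. Allowing for the cut grid, the range is about 7 to 16.

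**5. Proportional odds.** Odds ratios 1.5 to 2.5, 60 to 135 per arm, assumed distributions, best cut:

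| Outcome | Loss (points) |
|---|---|
| MMSE-like | 2.8–11.8 |
| FIM-like | 2.5–12.3 |
| Drug count (five levels) | 3.6–13.1 |
| Seizure count, 65–80 % with none | about 0–3.4 |

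At the plan's own odds ratio of 2.25 with 108 per arm, the MMSE distribution of step 4 gives 91.7 % on the full scale against 84.1 % at the best cut, a loss of 7.6 points.

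**6. Primary outcome, for comparison.** With 40 % against 60 %, a common odds ratio of 2.25, 20 % control mortality, 135 per arm and a final critical value of 1.977, power is 90.3 % for the binary GOS and 94.2 % for an ordinal GOS. The gain is 3.9 points.

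**The case against.** **The article may be using shorthand.** One bullet mixes an event, counts and scores under a single heading, and the statistical section names functional impairments rather than MMSE or FIM. The aim is itself worded as presence of impairment. This has some force. Still, both sections speak of percentages, the method named is logistic regression, and no graded analysis is given for these outcomes.

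**Cut-offs may be in the full protocol or SAP.** Correct. A reader might infer that missing cut-offs are a defect, or that a badly placed cut would lose far more power. Neither is argued here: the article names no cut, and the losses above are taken at the best one.

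**The loss may be small.** It is model-dependent. A reader might infer a loss of up to 20 points for all four outcomes. The documents do not support that. The figure needs normal scores without a ceiling, and it fails for seizure counts that are mostly zero, where any-versus-none keeps nearly all the information.

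**A binary outcome can count deaths as impaired.** The article does not say that it does so, but the underlying point stands. The scored patients are survivors, so a full-scale comparison without a rule for deaths would be a survivors-only comparison, in a trial analysed by intention to treat. The fix has to include that rule.

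**These outcomes are secondary and unpowered.** True, and this limits the weight of the point.

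**Conclusion.** The point holds for MMSE, FIM and number of antiepileptic drugs. As stated, the plan compares graded data as percentages. At the best cut this costs:

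- **MMSE and FIM:** roughly 3 to 16 points of power (about 3 to 12 under proportional odds, about 7 to 16 under a normal shift with a ceiling).
- **Drug number:** roughly 4 to 13 points.
- **Seizure frequency:** no power claim, since the loss is about 0 to 3 points if most patients have none.

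Every distribution and the number scored are assumptions. The figures for MMSE and FIM describe scored survivors and were not recomputed with deaths ranked. A reader might extend the criticism to the binary primary GOS. The gain from an ordinal analysis there is only about 4 points under the plan's own assumptions, and no point is made of it. The primary conclusion is unaffected.

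**What to change.** 1. In the statistical methods for secondary outcomes, keep logistic regression for the yes/no outcomes: recurrence of status epilepticus, mortality, EEG seizure, refractory status epilepticus and any seizure.
2. Compare MMSE, FIM and number of antiepileptic drugs on their full scales with a proportional-odds (rank-based) model, using the same covariates as the other models.
3. State a rule for deaths. For example, rank death as the worst category for MMSE and FIM, with a survivors-only analysis as supportive, and say how deaths are handled for drug number.
4. Reword the list of secondary outcomes so that it names the scores and the count themselves. Keep percentages impaired as description.

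The cost is wording only; no new data, visits or patients are needed. The small downside is that a common odds ratio is less direct to read than a difference in percentages, which the descriptive percentages offset. The article reports that analysis was still under way and allows changes to the analysis plan if they are justified in the final report.

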### Aims

The main study objective is to evaluate the effectiveness of therapeutic hypothermia (32–34 °C) for 24 h in decreasing 90-day morbidity and mortality, defined as a GOS score <5, in patients with CSE requiring ICU admission and mechanical ventilation.

The secondary objectives are to evaluate the effectiveness of therapeutic hypothermia (32–34 °C) for 24 h in decreasing seizure duration, progression to refractory CSE, ICU mortality, hospital mortality, 90-day mortality, hospital stay length, and 90-day functional impairments (motor and/or cognitive impairment, epilepsy).

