### Standardised anticonvulsant treatments after randomisation in both groups

To be eligible, patients should have received at least one of the first-line anticonvulsant drugs (clonazepam and diazepam) listed in French guidelines. Patients with ongoing motor seizures who have not received a second-line anticonvulsant (fosphenytoin, phenytoin, phenobarbital, or sodium valproate) before randomisation receive a loading dose of one of these drugs selected according to the indications and specific contraindications of each [33].

Patients with refractory CSE, defined as CSE persisting despite two lines of anticonvulsant therapy within 60 min, are given an intravenous 2 mg/kg propofol bolus followed by an additional intravenous 1 mg/kg bolus every 5 min until motor seizures stop, at which point a continuous intravenous propofol infusion is started at a rate of 2–5 mg/kg/h. In patients with uncontrolled refractory CSE despite continuous intravenous propofol at a rate of 5 mg/kg/h, anaesthetic drugs (midazolam or thiopental) can be added.

CSE must be controlled within 60 min after randomisation in both groups and before the induction of therapeutic hypothermia in the experimental group.

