### Data collection and follow-up

The following baseline characteristics are recorded at admission: age, sex, date and time of ICU admission, McCabe score and Knaus score, and pre-existing comorbidities. The Simplified Acute Physiology Score II is computed 24 h after ICU admission.

The study protocol also requires collection of the following data:Description of the CSE: circumstances of onset, date and time of onset and of seizure control, clinical features of seizures, pre-hospital and hospital providers and timing of anticonvulsant and supportive treatments, results of aetiological investigations (brain CT, lumbar puncture, MRI, laboratory tests including toxicological screen), aetiological diagnosis, type and dosage of antiepileptic drugs, and date and start and stop times of continuous EEG monitoring;Data related to ICU and hospital management: description of the acute disease; description of organ failures according to the Logistic Organ Dysfunction score (at inclusion and on days 0, 1, 2, 7, 14, and 28); use of mechanical ventilation, inotropic support, and/or renal replacement therapy; vital and functional status at ICU and hospital discharge according to the GOS; and cause of death (treatment limitation decision, refractory SE, and/or ICU complications);Data related to therapeutic hypothermia: modalities of induction and maintenance; core temperature every 4 h during the first 48 h; serum levels of creatine phosphokinase, triglycerides, and electrolytes; arterial lactate and blood gas levels; electrocardiogram; occurrence of aspiration pneumonia; and results of blood cultures on samples taken within the first 24 h;Data related to outcomes: 90-day GOS score by structured phone interview and neurologist visit; description of functional sequelae; mini–mental state examination (MMSE) score; and Functional Independence Measure scale (FIM) score.

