Several key points of the trial design received special attention and deserve discussion. First, our focus on patients with CSE requiring ICU management is warranted by reports of severe functional impairments after CSE. Indeed, the main objective of the study is neuroprotection, as opposed to only seizure control. We hypothesised that early implementation of our neuroprotective strategy in comatose patients after the control of CSE would translate into improved 90-day outcomes. We therefore decided to include not only patients with refractory CSE, but also all patients remaining comatose after control of motor seizures. Similarly, we planned to include patients regardless of the underlying aetiology even if this may lead to heterogeneity. As we were unwilling to require the use of mechanical ventilation for the trial, we included only patients who needed mechanical ventilation for any medical reason after CSE. Second, the choice of 32–34 °C as the therapeutic hypothermia target rests on both data from experimental animal models of SE and current practice regarding the use of therapeutic hypothermia in various conditions such as coma after cardiac arrest, stroke, or even traumatic brain injury [27, 36, 37]. Finally, the 24-h duration of therapeutic hypothermia after CSE control is based on the current standard of care for refractory SE, which includes anaesthetics for up to 24 h with a burst-suppression EEG pattern [5, 32]. Third, therapeutic hypothermia requires sedation and neuromuscular blockade. To ensure patient awakening as early as possible after the end of the neuroprotective procedure, we chose drugs with short half-lives, such as propofol and cisatracurium. Propofol has the additional advantage of exerting anticonvulsant effects. However, we felt it would be unethical to require the use of sedation in patients in the control arm. Thus, the continuation of sedation in controls is at the discretion of the bedside physician. Finally, safety considerations led us to limit the use of propofol to 48 h with an infusion rate no greater than 5 mg/kg/h, in both arms [38]. Fourth, we chose the 90-day GOS score as the primary outcome. The GOS is used chiefly to evaluate overall outcomes of neurological conditions [39–41]. The GOS in its structured form has been found valid, practical, and reliable [42]. It also has the advantage of having been used in several studies of SE, and it is well suited to an assessment of the physical and functional burden after CSE [43]. Moreover, in the preliminary work that allowed us to formulate the hypothesis for the sample size estimation, the 90-day functional outcome was evaluated using the GOS [4]. Importantly, the GOS has been found valid, practical, and reliable [42, 44].

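### Seizure duration is tested as an effect of hypothermia, although the protocol requires convulsive status to be controlled before cooling; patients already refractory at randomisation are not separated from those who progress

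*Protocol article*

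**What the plan says.** All references are to the protocol article.

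- **Aims.** The secondary objectives are effects of hypothermia and include "decreasing seizure duration, progression to refractory CSE".
- **Study outcomes, Secondary outcomes.** The list includes total seizure duration in minutes and the percentage of patients with refractory SE. No start, end or time window is given for either.
- **Statistical methods, Secondary outcomes.** "To compare seizure duration (in minutes), we will build a semi-parametric regression model (Cox or Fine–Gray", with the competing events given as "control of SE vs. death without control of SE". Refractory SE is analysed by logistic regression, in a sentence that refers to EEG evidence and to the period after randomisation.
- **Standardised anticonvulsant treatments.** "CSE must be controlled within 60 min after randomisation in both groups and before the induction of therapeutic hypothermia in the experimental group". Refractory status is defined here too: "Patients with refractory CSE, defined as CSE persisting despite two lines of anticonvulsant therapy within 60 min".
- **Therapeutic hypothermia group.** There is a separate sedation instruction for patients who were refractory before randomisation, so such patients are enrolled.
- **Discussion.** Enrolment covers refractory patients "but also all patients remaining comatose after control of motor seizures".
- **Randomisation.** Seizure duration, cut at 60 minutes, is a stratification factor.
- **Data collection.** The form records "date and time of onset and of seizure control".

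**The concern.** An outcome can measure the effect of a treatment only if it can still change once the treatment starts. Here the modelled event is control of SE, and the treatment section places control of the convulsive episode ahead of cooling. Part of the interval, and for some patients all of it, lies before randomisation. The protocol itself uses seizure duration as a baseline factor when it stratifies on it.

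The risk is misreading in both directions. A null result could be reported as evidence that hypothermia does not shorten seizures, which this comparison cannot test. A positive result could be credited to cooling when it must come from something else: chance, baseline imbalance, or care between randomisation and cooling. That care is open-label, with propofol sedation prescribed in one arm and left to the bedside physician in the other.

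A narrower version applies to progression to refractory CSE. A patient who is refractory at entry cannot progress to that state, yet the plan does not separate such patients from those who become refractory later.

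**Working it through.** The plan gives no figure for this point, so the check sets its timing rules beside its outcome definitions.

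**1. Timeline of the index convulsive episode in a patient managed to protocol**

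- Onset to randomisation: at most 8 h (Study population; Table 1), which is 8 × 60 = 480 min.
- Randomisation to control: at most 60 min (Standardised anticonvulsant treatments).
- Start of cooling: after control (same section).
- Longest possible index episode: 480 + 60 = 540 min. Minutes of it after cooling starts: 0.

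**2. Does the time origin matter?** The article does not state it.

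- From seizure onset, the interval contains all the pre-randomisation time and ends before cooling.
- From randomisation, it is at most 60 min. For patients whose seizures had already stopped, the event precedes the origin.

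Under either origin, the event comes before cooling.

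**3. Refractory status**

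- By the treatment-section definition (two drug lines, 60 min), some patients meet it before randomisation, and the hypothermia section provides for them.
- EEG-evidenced refractory SE after randomisation is different. Continuous EEG starts within 2 h of randomisation and runs for 48 h and/or until temperature normalises. It therefore covers the cooling period, and the general management section foresees refractory CSE or non-convulsive SE on it. Such events can follow cooling.

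**4. Illustration of dilution (assumed inputs, not from the documents)**

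There are 135 patients per arm and time runs from randomisation. A share q is still uncontrolled at 60 min; the rest are controlled at a uniform time between 0 and 60 min. For the share q, the further time to control is exponential with mean 60 min in controls. Cooling multiplies the hazard of control by 1.5 in these patients only. Deaths are ignored. Each row is 300 simulated trials analysed by Cox regression.

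| Share uncontrolled when cooling starts | Average hazard ratio | Trials with p < 0.05 |
|---|---|---|
| 0% (rule followed) | 1.00 | 6.7% |
| 10% | 1.04 | 6.3% |
| 25% | 1.09 | 9.7% |
| 50% | 1.21 | 33% |
| 100% | 1.52 | 90% |

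The simulation error around a true 5% is √(0.05 × 0.95 / 300) = 1.3 percentage points, so 6.7% is compatible with the nominal rate. If the rule is followed, a genuine 1.5-fold effect on control is invisible. With one patient in ten still uncontrolled, the effect remains close to invisible. The documents do not give the true share, so the table shows a range and not an estimate.

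**The case against.** The strongest reply has four parts.

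- **Convulsive status is not all status.** The control-before-cooling rule concerns CSE, whereas the modelled event is control of SE. Non-convulsive SE can persist or emerge during cooling, and total duration might be meant to include recurrences. This is possible, but the article does not say so. The model has a single control event, and the form is described as recording onset and control. The point is therefore limited to the index convulsive episode.
- **The rule is a requirement, not a fact.** The same section plans for uncontrolled refractory CSE, the model allows for death without control, and analysis is by intention to treat. Some patients may depart from the sequence. Moreover, the Abstract describes the strategy as hypothermia with routine propofol, so an arm difference could partly reflect the assigned strategy. This stands. A reader might infer that the hazard ratio must be about 1 by construction, but the text does not establish that. What follows is only that a difference in protocol-compliant patients would not be an effect of cooling, which is what the Aims claim to measure.
- **Refractory SE is analysed on EEG after randomisation.** A reader might infer that this outcome too is settled before treatment. The statistical section, read with the EEG schedule, does not support that. Only the mixing of already-refractory and newly refractory patients remains.
- **A post-randomisation seizure outcome already exists.** Recurrent convulsive or non-convulsive seizures between 6 and 12 h are listed and tested. This is correct and limits the damage, but it does not rescue the seizure-duration comparison.

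Two further inferences should be avoided. The documents give no frequencies, so it cannot be said that many patients are controlled, or often refractory, at entry. Left truncation would require a time origin at seizure onset, and no origin is stated.

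**Conclusion.** The concern holds for seizure duration and, more narrowly, for progression to refractory CSE. In patients managed as the protocol requires, the length of the index convulsive episode is settled before cooling, and for those already controlled at entry it is settled before randomisation. The secondary comparison of time to control therefore cannot show an effect of cooling, and a null result says nothing about an anticonvulsant effect. Patients already refractory at randomisation cannot progress to that state. EEG-evidenced refractory SE arising after randomisation remains a legitimate outcome.

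This rests on two assumptions: that the control-before-cooling rule is followed, and that control of SE refers to the index convulsive episode, which is the most direct reading of the article. If the full protocol defines the event more broadly, the article should say so. The matter affects secondary outcomes only. The primary outcome (90-day Glasgow Outcome Scale score) and the sample size of 270 do not depend on it.

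**What to change.** 1. **Reconcile the sections.** The Aims, the treatment sequence and the two Secondary outcomes sections should agree on what seizure duration means (convulsive or any SE, start, end) and on the window for refractory SE. This concerns outcome definitions only; no change of treatment rule is proposed.
2. **Replace total seizure duration as an effect outcome.** Use post-randomisation seizure burden, or time to first recurrent convulsive or electrographic seizure or SE on the continuous EEG. Count from randomisation in all randomised patients, with death as a competing event, over the same 48 h in both arms. Burden is defined for everyone; time to recurrence needs a stated rule for patients still convulsing at randomisation. Counting from a later landmark, such as 60 min, would condition on what happened after randomisation and is better avoided.
3. **Use pre-randomisation seizure duration only as a baseline covariate.**
4. **Analyse new refractory SE after randomisation among patients not refractory at randomisation.** This is a baseline subgroup, so the randomised comparison is preserved.
5. **Guard the interpretation.** If time to control is still reported, label it as descriptive of early care, not as an effect of cooling.

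**Cost.** Onset and control times and continuous EEG are already collected, although recurrences across the 48 h may need further EEG reading. There will be fewer countable events, and starting at randomisation keeps some pre-cooling minutes in both arms, which dilutes any effect. Enrolment was complete and analysis under way when the article was written, so the change must be documented and justified before unblinded analysis. The Statistical methods already require any change to the analysis plan to be justified in the final report.
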